### Participants – clinicians

Clinicians working within the Counselling, Marijuana Clinic and MERIT teams will be invited to participate in the study. At a minimum, these clinicians will have a tertiary education in a counselling-related field, with at least an undergraduate degree in nursing or psychology.

### Participants – clients

All clients, new and ongoing, will be invited to partake in the study. Participants will be aged 18 years and over and residing on the Central Coast and surrounding areas of New South Wales. Participants will consist of individuals attending counselling with primary presenting issues related to substance abuse or dependence. No exclusion criteria will be applied to participants (e.g. comorbid conditions), and it is expected that at least 50% of the clients will be experiencing co-occurring depression or anxiety and many will be poly-drug users. In 2006-7, 2,632 calls were received by the central intake service for the Area Health Region in which the Central Coast DACS is located, with 64% of these being referred to Central Coast DACS. Within the service, 3,329 treatment episodes were commenced, with 73% of clients completing treatment 
[19]. The majority of these (61%) were for males, aged 20-39 years (51%), with alcohol being the most common primary drug of concern (49%).

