## Background

Mounting pressure is exerted on the health system by the increasing prevalence of depression and alcohol/other drug (AOD) misuse. These disorders are ranked 3 and 17 in contribution to the global disease burden, with depression elevated to 1st place and alcohol abuse use to 5^th^ among middle-high income countries such as Australia 
[1]. Efficacious treatments have been tested with success for both depression 
[2] and AOD disorders 
[3], suggesting that this burden can be reduced.

Despite this, the gap between need for and receipt of these treatments is large, particularly for counselling 
[4], which is often preferred over pharmacotherapy 
[5]. For example, in the US, 2.1 million people with a 12-month mental disorder did not use services for mental health problems but perceived they had an unmet need 
[6]. Of these, the highest unmet need was for counselling 
[6]. Comorbidity, or the co-occurrence of two or more disorders, is the rule rather than the exception in clinical practice 
[7], with up to 89% of people with AOD use disorders also experiencing depression 
[8]. The presence of comorbid disorders compounds difficulties in treatment access and provision 
[9].

Mental health and AOD researchers and clinicians must respond to these issues, by developing and evaluating treatment programs that address depression and AOD use disorders, whilst minimising cost and maximising efficient use of clinician time and client outcomes. Available evidence-based treatments provide for single problems (e.g. depression or alcohol misuse) rather than the comorbidity with which clients typically present 
[7]. Treatments are often high intensity, require specialist input and training, and are therefore only accessible to a minority of clients 
[10]. For these reasons, many clinicians are not able, or willing, to implement these interventions in practice.

The increased availability and use of computer/internet-based programs as a supplement to health care is also a potential solution to well-documented treatment accessibility problems 
[11], particularly among people with depression and AOD use comorbidity. Interactive and multimedia options offer the potential for higher levels of engagement than other self-help modalities 
[12]. Computers/the internet offer the opportunity for widespread dissemination of treatments, reaching a large audience in a cost effective and timely manner 

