### Statistical analyses

#### Clients

For the client sample, primary outcome measures are changes in depression, alcohol and marijuana use between baseline and 12-week follow-up.

Previous research using the SHADE resource among substance users 
[16] has resulted in effect size differences of 0.42 between clients exposed to the SHADE resource versus not on depression, alcohol and marijuana use. Assuming similar effect size differences will apply to the current study, we estimate that a sample size of 72 is required at 15-week assessment to achieve adequate power (power = 0.81) to detect differences of this order using repeated measures analysis of variance with an alpha level of 0.05 (calculated using G*Power, version 3.1.2). Predictors of alcohol use, marijuana use and depression at 15-weeks relevant to the current study (e.g. client rated therapeutic alliance, internal and external motivation and coerced vs non coerced clients, exposure to SHADE) will be modelled using a linear regression analysis. This sample size will also enable us to examine an effect size of 0.15 for a linear multiple regression for these outcome variables, with up to 6 predictors, an alpha level of 0.05 and a power co-efficient of 0.80 (actual sample size required = 98).

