## Discussion

This will be the first real world dissemination trial of the SHADE computerized resource; shown in previous research to be efficacious in reducing depressive symptoms, alcohol and cannabis use among people reporting these comorbid problems, under controlled research trial conditions 
[16]. We will seek to establish the success with which the SHADE resource is translatable to a publicly-funded Drug and Alcohol Clinical Service. Bennett and Glasgow 
[28] have recommended the RE-AIM framework 
[29] as one that includes the critical factors in disseminating technology-based interventions from the research to the clinical setting. The RE-AIM factors are:

(a) Reach: report on the number and percent of participants (eligible, consenting, representativeness);

(b) Effectiveness: the change in key outcomes associated with the intervention;

(c) Adoption: report on the number and representativeness of staff in the clinical setting who consent to participate in the dissemination trial;

(d) Implementation: how the program is delivered, and whether there is consistency in delivery;

(e) Maintenance – individual: long-term effects on individual outcomes; and

(f) Maintenance – setting: sustainability of implementation of the program following completion of the trial.

The current study will cover the first four critical factors (Reach, Effectiveness, Adoption and Implementation), and over the longer term will seek approval to monitor continued use of the SHADE resource in the target Drug and Alcohol Clinical Service. In doing so, it will address several key recommendations important in achieving the goal of widespread dissemination of technology into clinical practice 
[28].

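### The 0.42 effect comes from clients with both depression and substance problems but is applied unadjusted to change in depression in an unselected sample, so power for depression may be lower than stated and baseline severity needs to be modelled

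*Protocol article*

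**What the plan says.** **Entry.** Under Participants – clients, the protocol article states: "Participants will consist of individuals attending counselling with primary presenting issues related to substance abuse or dependence". It sets no depression criterion, and about depression or anxiety alongside the substance problem it adds: "No exclusion criteria will be applied to participants (e.g. comorbid conditions), and it is expected that at least 50% of the clients will be experiencing" one or the other. The Background gives a higher figure for depression alone: "with up to 89% of people with AOD use disorders also experiencing depression".

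**Outcome and effect.** Under Statistical analyses, Clients, the "primary outcome measures are changes in depression, alcohol and marijuana use between baseline and 12-week follow-up", for the client sample as a whole. Earlier research "has resulted in effect size differences of 0.42 between clients exposed to the SHADE resource versus not on depression, alcohol and marijuana use". The article assumes that similar effects will apply here and derives a need for 72 clients (power 0.81, alpha 0.05, repeated measures analysis of variance). Sample size calculation projects 100 retained.

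**Source of the effect.** Statistical analyses describes the earlier sample only as substance users. The Background says that the same work concerned concurrent depression and substance use disorders, and the Discussion describes SHADE as "shown in previous research to be efficacious in reducing depressive symptoms, alcohol and cannabis use among people reporting these comorbid problems".

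**Baseline depression and exposure.** Study aims names primary drug of concern, coercion and computer comfort as moderators, but not baseline depression. The section on clinicians under Study design leaves it to them how, when and with whom SHADE is used. The DASS-21 is collected at baseline and follow-up.

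**The concern.** The effect was estimated where depression was part of the presenting problem. It is then used for depression in a sample where depression is optional. A client with a low baseline depression score has little room to improve. If such clients gain less from SHADE, the average effect in this sample is smaller than 0.42 and the stated power for depression is too favourable. A null result could then reflect case mix, not failure of SHADE in the people it was built for.

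The second issue is bias. Exposure is the clinician's choice. If SHADE goes more often to clients with higher baseline depression, those clients also have more room to fall and more regression to the mean. A comparison of raw change between exposed and unexposed clients would credit that to SHADE. If SHADE goes more often to clients with lower baseline depression, the error runs the other way.

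**Working it through.** **Inputs from the article:** effect 0.42; 72 clients for power 0.81; alpha 0.05; projected retained sample 125 × 0.80 = 100; at least 50% with depression or anxiety; up to 89% with depression.

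**Inputs assumed:** p, the share of clients with depression to improve; r, the effect in the other clients as a fraction of 0.42; the same p in exposed and unexposed clients; equal standard deviations. The article gives none of these. I vary p and r.

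**Step 1: the stated figure.** The 72 cannot be confirmed, because the article does not give the correlation between time points or say which effect-size metric 0.42 is. Read as a standardised mean difference (f = 0.21, two groups, two times), the group-by-time test at 72 has power 0.94 at a correlation of 0.5, and 0.81 only at a correlation of about 0.23. So I take 0.81 at 72 as given and calibrate to it. The results below then do not depend on the missing correlation.

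**Step 2: calibration.** A two-group F test with 1 and 70 degrees of freedom has power 0.81 when the noncentrality is 8.28, which is 8.28 / 72 = 0.115 per client. At 100 clients and the full effect it is 11.5, giving power 0.92.

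**Step 3: dilution.** The whole-sample effect is 0.42 × s, with s = p + (1 − p) × r. The noncentrality at N clients is 0.115 × N × s².

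With r = 0, s = p:

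| Depressed share p | Whole-sample effect | Noncentrality at 100 | Power at 72 | Power at 100 | Clients needed for 0.81 |
|---|---|---|---|---|---|
| 0.50 | 0.21 | 2.88 | 0.30 | 0.39 | 283 |
| 0.60 | 0.25 | 4.14 | 0.40 | 0.52 | 197 |
| 0.75 | 0.32 | 6.47 | 0.57 | 0.71 | 127 |
| 0.89 | 0.37 | 9.11 | 0.71 | 0.85 | 91 |

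With r = 0.5 and p = 0.50, s = 0.50 + 0.50 × 0.5 = 0.75, which is the third row: power 0.57 at 72 and 0.71 at 100.

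**Step 4: how much dilution the plan can absorb.** Noncentrality scales with N × s², so 100 clients match 72 undiluted clients when s = √(72/100) = 0.85. The margin between 72 and 100 covers a loss of about 15% of the effect and no more.

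**Step 5: baseline severity.** With two time points, the group-by-time term in a repeated measures analysis of variance compares mean change between groups. It does not adjust for a difference in baseline depression between exposed and unexposed clients. The article's linear regression might do so, but its predictor list is illustrative and does not name baseline depression.

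**The case against.** Open enrolment and a service-wide average are legitimate here. The study observes use of SHADE in a real service, and its hypothesis compares exposed with unexposed clients without restriction to the depressed. This stands. A reader might infer that the depression outcome is set in the wrong population and should be confined to depressed clients; the documents do not support that. Such a contrast would also have its own cost: with p = 0.50 it leaves 50 clients, fewer than the 72 required, with power of about 0.65 on the same calibration.

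A reader might also infer that only about half the clients are expected to be depressed. The article says at least 50%, which is a floor. That floor pools depression with anxiety, so the depressed share could be higher or lower; at the 89% cited in the Background, the projected 100 would still have power of about 0.85. Nor does the article show that dilution will occur: it gives no baseline distribution of depression scores, and a client without a depressive disorder need not be at the bottom of the scale.

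That clinicians will direct SHADE to the more depressed is likewise conjecture, since the uses that they suggested do not mention it. Finally, covariates and interactions are often left to an analysis plan that is not shown. But the article itself fixes the outcome, the population, the borrowed effect, the sample size and the power, and it is these that do not fit together.

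**Conclusion.** The point holds as a caveat on power and on the form of the depression analysis. The article carries 0.42 from a comorbid sample to an unselected one without comment, and its comparison of change makes no stated allowance for baseline depression.

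The size depends on two unknowns. With no effect in non-depressed clients, power at 100 runs from about 0.39 at a depressed share of 50% to about 0.85 at 89%. With half the effect in the others and a share of 50%, it is about 0.71. The plan keeps its stated 0.81 only if about 85% of the 0.42 survives. All of this rests on accepting 0.81 at 72, which could not be confirmed, and on equal standard deviations. It concerns depression only; these figures say nothing about alcohol or marijuana use. Bias from selective use is possible, but its direction and size cannot be judged from the article.

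**What to change.** Keep open enrolment, and keep the whole-sample depression contrast as primary. In Statistical analyses, Clients:

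1. Estimate the contrast from a model of follow-up DASS-21 depression with SHADE exposure and continuous baseline DASS-21 depression.
2. Prespecify the exposure-by-baseline-depression interaction. Report the estimated SHADE difference at a prespecified elevated baseline depression score as a key supporting result.
3. State that 0.42 comes from people with both depression and substance problems, and quote power for depression over a range of depressed shares, with the assumed effect in the other clients, as in the table above.

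**Cost.** No new data are needed, because the DASS-21 is already collected at both times. The model gains an interaction term, which 100 clients will estimate imprecisely, and the stated power for depression becomes less favourable. Adjusting for baseline depression does not remove other confounding from clinician-chosen exposure.

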### Study design

This study is designed to observe, and not prescribe, the use of the SHADE computerized treatment program within the Central Coast DACS. Ethics approval for the study has been obtained from several relevant Human Research Ethics Committees, led by the Northern Sydney Central Coast Human Research Ethics Committee (08/HARBR/78/79), and including the University of Newcastle Human Research Ethics Committee (H-2008-0271), and the Macquarie University Ethics Review Committee (Human Research, 0806-125M(R)).

#### Clinicians

At information sessions conducted by the authors, clinicians in each team associated with the DACS were introduced to the study and asked to provide consent to participate. Participation involves five activities:

(1) Completion of a baseline focus group discussion regarding the use of innovation in clinical practice.

(2) Completion of a baseline questionnaire regarding their openness to innovation and computer comfort.

(3) Use of the SHADE treatment program with new and ongoing clients in whatever manner they choose, with delivery of the DVD content of the program either contained within the clinic session or provided to clients to complete in their own home in between clinic sessions.

(4) Referral of contact details for new and ongoing clients to the client-data-collection phase throughout the study period, regardless of their exposure to the SHADE treatment program.

(5) Completion of session checklists (see Appendix A) following every counselling session with new and ongoing clients, regardless of their exposure to the SHADE treatment program, and therapeutic alliance measures at intake and discharge for all clients.

Clinicians are provided with a half-day tutorial on the SHADE resource conducted by the research team. The content of this tutorial includes a discussion of the results of the previous clinical trials conducted using the SHADE program, and orientation to the SHADE resource. Clinicians split into groups of two and worked through a different SHADE module on laptops provided by the research team. At the conclusion of this session, clinicians presented each module to the group, and discussed ways in which they felt the module could be integrated into their clinical work at the DACS. Researchers provided their own input into this session where relevant. There was no prescription provided to clinicians as to how, when or with whom the SHADE resource should be used with their clients. However, clinicians suggested that they would use it in the following ways:

(a) “Prescribe” modules for homework in between in-person sessions;

(b) Complete individual modules during the session, sitting side-by-side with clients;

(c) Provide the SHADE resource on DVD-Rom to clients on the wait-list for the DACS;

(d) Use the handouts and worksheets from SHADE to augment discussions about cognitive behavioural skills conducted between clients and clinicians during sessions;

(e) Use of the video and audio material to supplement the relapse prevention group program conducted by the DACS.

### Current/ongoing clients

Following the provision of contact details to the research team via their clinician, current and ongoing clients of the DACS are contacted to discuss consent to participate in the study. Once consent is established, clients complete a baseline and 12-week follow-up assessment delivered over the telephone by research assistants independent from the DACS. Clients are reimbursed $20 AUD for each completed assessment.

### The SHADE treatment program

The SHADE treatment program has been described elsewhere 
[16,20], and incorporates CBT and ME strategies to encourage reductions in depression and AOD use. The program is available in two formats: (i) a 10-session program designed to be completed in a linear fashion, once weekly for 10 weeks, with content pre-programmed for each session; and (ii) a skill module program, where a series of shorter modules are presented based on themes related to depression and AOD use problems (e.g. coping with cravings, taking charge of my thoughts, staying well) arising from the 10-week program. Clients and/or clinicians may choose to focus on just one skill module during a session, without having to complete the other skills and strategies contained in the resource. Both versions of the SHADE program appear on the one DVD-Rom from which the program operates. Text is pitched at a reading age of 14 years, with a voiceover available to read out all text contained in the resource. Video case scenarios guide clients through a range of skills and strategies, and a range of handouts and worksheets are also available for clients/clinicians to print out and use during a session or as a homework activity.

### Assessments

All assessment instruments are widely used in mental health and/or AOD treatment research and practice.

#### Clinicians

Clinicians will participate in a baseline focus group discussion designed to elicit their attitudes and concerns about adopting innovation into their clinical practice in general, and the SHADE treatment program in particular. Table
1 displays the structure of this focus group discussion.

**Table 1 T1:** Clinician focus group protocol

	
(1)	What sources do you use to inform your clinical practice (e.g. journals, workshops, clinical guidelines)?
(2)	What influences you in deciding on when to use a particular strategy, technique, or resource during a session with a client? How do handouts, self-help books and other information for clients fit into this process?
(3)	Have you incorporated any technology into your sessions with clients already? How did you do that, and what was the result?
(4)	Are there any advantages to using technology, e.g. SHADE, as an adjunct to your clinical practice? And what might the disadvantages or concerns be? What are the main issues?
(5)	What are some of the supervision and supports you think that you might need to have in place to assist you in using technology in your clinical practice?

Subsequent to completing the focus group discussion, clinicians complete two further self-report measures:

(1) Innovativeness Scale 
[21]: a 20-item measure using a 7-point Likert-type scale assessing the likelihood of an individual to adopt innovative strategies in their work.

(2) Computer Opinion Survey 
[22]: a 26-item measure using a 6-point Likert-type scale, developed as a measure of the trait of computer anxiety rather than the “state” of computer anxiety.

During the course of the study, clinicians complete a session checklist at the conclusion of each session with a client, which outlines the focus and content of the session, including whether or not SHADE or other technologies were used. The checklist was developed by the authors to specifically suit the Central Coast DACS and the range of counselling interventions applied by the clinicians. At the conclusion of each counseling session, clinicians complete a series of tick boxes to report on: the session orientation (initial appointment, assessment, scheduled appointment, non-scheduled client contact, discharge/final session), the intervention applied, whether multimedia was used during the session (if no, why not; if yes, specify the type, e.g. SHADE, and the way in which it was used), whether debriefing was held in relation to the multimedia used with the client, and an approximation of the length of time multimedia was discussed during the session. Please see Appendix A for a copy of the session checklist.

At intake and discharge with a client, clinicians also complete the therapist scale of the Agnew Relationship Measure 
[23]. This scale asks clinicians to rate, on a 7-point Likert scale, 28 items relating to the extent to which they feel a bond, partnership, confidence, openness, and client initiative are features of the therapeutic relationship with their client.

#### Clients

Following the provision of consent, clients complete the following set of assessment measures at baseline and 12-weeks post-baseline via telephone with a trained research clinician, who is independent of the Central Coast DACS. The following questionnaires take between 30-45 minutes to complete:

(1) Demographics: information includes age, gender, occupational and marital status, children, educational experience, ethnicity and current accommodation arrangements.

(2) Service Utilisation: includes current and previous treatments, including self-reported hospitalisations, attendance at clinics, rehabilitation programmes, contact with community mental health teams, psychologists, psychiatrists, other health professionals, involvement in AOD detoxification and counselling, methadone maintenance, 12-step programmes, use of general practitioners, and use of medication (including compliance).

(3) Opiate Treatment Index 
[24]: a quantity/frequency index to estimate average daily use of 11 drug types (alcohol, marijuana, heroin, other opiates, amphetamines, cocaine, hallucinogens, barbiturates, tranquilisers, inhalants and tobacco) in the month prior to assessment.

(4) Treatment Motivation Questionnaire: is a 26 item self-report measure, examining four components of motivation including internal and external motivation, help seeking and confidence in treatment. A 7-point Likert scale is used to examine the level of motivation.

(5) Depression Anxiety Stress Scale 21-item version 
[25]: a 21-item screening tool to for depression, anxiety and stress in the previous 7 days. A 4-point Likert-type scale is used to determine the extent to which a symptom applied to the person.

(6) Global Assessment of Functioning 
[26]: a clinician-rated assessment of current functioning.

(7) Self-compassion Scale 
[27]: is a 26-item measure using a 5-point Likert-type scale assessing the extent to which a person expresses self-compassion towards themselves in difficult times.

(8) Agnew Relationship Measure – Client Version 
[23]: this client-rated measure of therapeutic alliance is similar in content and structure to the therapist-rated version previously described.

We plan to report the cost of delivering the intervention in real world settings and the cost impacts of the outcomes achieved by calibration of selected instruments used in the study (e.g. Quality of Life Scale, Global Assessment of Functioning) with those achieved in other costing studies.

